### Participants and sample size

Eligible participants are aged between 10 and 21 years and meet the criteria for depressive disorders, based on DSM-5 [51]. Inclusion is based on a structural clinical interview (Kinder-DIPS, parent or child version [52]). A participating caregiver is mandatory in the CBASP@YoungAge group, whereas caregiver participation in the TAU groups is not requested beyond the legal requirements. As psychotherapy is conducted in German, children and participating parents need to be sufficiently fluent in German. Further, sufficient cognitive level of participating children/adolescents is required for the patients to be able to follow the cognitive interventions. Since intelligence tests are part of the standard diagnostics in the participating outpatient clinics, this criterion is operationalized by an IQ of ≥ 80.

We exclude children or adolescents in case of ongoing psychotherapy, acute suicidality, or a disorder expression requiring a different and non-depression focused treatment (e.g., traumatic disorder, schizophrenia, or bipolar disorders) or an inpatient stay. We do not exclude comorbid disorders or ongoing psychopharmacotherapy to enhance the external validity and generalizability of our findings. In case of outpatient housing, youth in the CBASP@YoungAge treatment group can nominate a different adult to participate in the sessions, as long as there is at least one significant person able and willing to join treatment sessions. If more than one person wants to participate, that is also possible.

Sample size calculations are guided by the considerations of Hertzog [53]. Thus, the planning of a larger study by this investigation was important, as well as the capacities of the centers involved and the sample size and drop out rate of other comparable studies [54, 55]. We aim to recruit 44 participants (22 per treatment arm). Assuming a 60% retention rate during the trial [56], this will lead 38 treatment completers with complete data.

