### Recruitment and procedure

Since the design is non-randomized, patients are consecutively recruited in the participating outpatient clinics. After initial appointments, therapists in the outpatient clinics identify and approach eligible patients based on the inclusion and exclusion criteria. They participate either in the CBASP@YoungAge treatment arm or in the treatment-as-usual control group (TAU). If screening indicates that the patient is eligible for participation and the family consents, complete study information is given to all participants, and written informed consent is obtained from the primary caregiver and participating child or adolescent.

Assessments are at baseline, post-treatment, and 6 months follow-up. During the treatment phase, a quantitative and qualitative orientated therapy process evaluation by therapist, patient, and caregivers is planned for every session, as is a quantitative evaluation of the general health index by patient and caregivers every 5th session. For detailed information on the study procedure, see Fig. 1 and for an overview of the actual study process and timeline Fig. 2.

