### Statistical analysis

A preliminary analysis of the results after post-assessment is planned. A full analysis will follow the completion of all follow-up assessments. Data will be analyzed based on the Intention-to-treat (ITT) sample and will help inform power calculations for a future CBASP@YoungAge randomized control trial.

Central aspects with regard to feasibility in the analysis are attrition and reasons for drop-out of patients or parents. These aspects will be recorded and analyzed. Recruitment rate is measured by reporting the number and reasons of patients screened for the intervention group who decided against study participation. We also capture the proportion of patients who participate in each arm at pre-, post- and 6-month follow-up assessment. Furthermore, we access the proportion of patients meeting criteria for response and remission based on the Kinder-DIPS at the different time points. With regard to attrition, therapists will assess the number of sessions of the modules, and the session frequency in general and related to the different modules. In addition, we will record each participant’s individual course of therapy in self-reports, and reports from others, as well as any unexpected events in the course of therapy. For participants who withdraw from the study, the researcher will follow-up with either the therapists or participants to document their reason(s) for study withdrawal. We will assess rates and types of missing data, and the proportion of drop-outs at different stages throughout the trial. We will also assess whether any of the measures display floor and/or ceiling effects. Patient adherence to treatment will be indexed by the mean (SD) number of therapy sessions offered and attended, and by calculating the proportion of participants who undergo a minimum adequate dose (eight or more sessions) in each arm. Adherence of protocol by therapists is analyzed descriptively by the proportion of complete adherence checks and the monitoring of individual case and data management in the study routine. Data completeness is reported as proportions of missing values. Due to sample size and this study’s pilot character, the feasibility analysis is mainly based on the intervention group’s process evaluation. First-interim analyses of results are only possible with sufficient post-measurements. Missing values will be integrated in an iterative imputation method based on a random forest model.

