We intend to carry out analyses with regard to effectiveness. Summary statistics will be used as appropriate to describe and compare data for all participants. ANCOVA models will be used to test the pre- and post-differences in the intervention group and the difference between intervention and control group after the intervention and at follow up. Within or between-group effect sizes (Cohen’s *d*) will be calculated and interpreted according to standard conventions (< .50 = small; .50–.80 = medium; > .80 = large [76]).

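### Random-forest imputation is followed by ANCOVA with no pooling stated; if it yields one completed data set, type I error, SD and raw effect are distorted, and pooling alone does not cure the effect shrinkage

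*Protocol article*

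**What the plan says.** All references are to the protocol article.

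- **Imputation (Statistical analysis):** "Missing values will be integrated in an iterative imputation method based on a random forest model". The number of completed data sets, a pooling rule, the predictors and the role of arm are not given.
- **Analysis set (Statistical analysis):** "Data will be analyzed based on the Intention-to-treat (ITT) sample", so patients without a post-treatment score stay in the analysis.
- **Model (Statistical analysis):** "ANCOVA models will be used to test the pre- and post-differences in the intervention group and the difference between intervention and control group". Cohen's d is then calculated.
- **Use of the results (Statistical analysis):** the data "will help inform power calculations for a future CBASP@YoungAge randomized control trial".
- **Size (Participants and sample size):** "We aim to recruit 44 participants (22 per treatment arm".
- **Expected loss (same section):** "Assuming a 60% retention rate during the trial [56], this will lead 38 treatment completers with complete data".
- **Visits (Recruitment and procedure):** "Assessments are at baseline, post-treatment, and 6 months follow-up".

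Under Outcomes, pre-post change in depressive symptoms, including the Mood and Feelings Questionnaire (MFQ), is a primary endpoint beside feasibility.

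**The concern.** A random forest fills a gap with a prediction, in effect a conditional mean. Predictions vary less than real outcomes. If one completed data set goes into ANCOVA as though all 44 outcomes had been measured, the residual variance is too small and the degrees of freedom too many, so standard errors are too small.

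The forest adds a second problem. With few patients and arm as one predictor among several, the trees seldom split on arm. Imputed values in both arms then drift towards a common mean and the between-arm difference shrinks. This is separate from the question of single or multiple imputation.

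At stake are the between-arm tests and the SD and effect estimates that the pilot is meant to hand on to the randomised trial.

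**Working it through.** **Expected loss.** 44 × 0.60 = 26.4 completers, about 13 per arm. The stated 38 is not reproduced: 38/44 = 86.4% retention, or 13.6% loss. Both rates are carried forward: 9 of 22 missing per arm (about 40%) and 3 of 22 (about 14%).

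**Assumptions not in the article.** Two-sided 5% test, outcome SD 1, pre-post correlation 0.5 (0.3 and 0.7 as variants), true effect 0, 0.36 or 0.50 SD. The 0.36 is the post-treatment effect size cited in the Background.

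**Hand check of the SD.** If 9 of 22 values are replaced by predictions of variance v, the SD is about √(13/22 + (9/22)v).
- v = 0 (predictions constant): √0.591 = 0.77.
- v = 0.25 (ideal linear prediction at correlation 0.5): √(0.591 + 0.102) = 0.83.
- With 3 of 22 replaced and v = 0: √(19/22) = 0.93.

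**Simulation A** (1,500 trials; 60 trees; predictors arm, baseline and four further baseline variables; one completed data set). At 40% loss, type I error was 10.5%, against 5.2% for complete-case ANCOVA. Mean model SE was 0.208 against an empirical 0.250, pooled SD 0.79 against 0.99. A true 0.36 was estimated as 0.27 (25% low), with 95% interval coverage of 86%. At 14% loss (1,200 trials): type I error 6.0%, coverage about 93%, SD 0.93.

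**Simulation B**, built separately (arm, age, three baseline and three post measures, the post measures missing together; 100 trees, 50 when imputed by arm; 600–1,500 null and 300–400 effect replicates; Monte Carlo SE of a null rejection rate about 0.6–1.1 points):

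| Method | Loss | Type I error | Mean estimate of a true 0.50 | Pooled SD |
|---|---|---|---|---|
| Complete-case ANCOVA | 40% | 4.0–5.9% | 0.50–0.52 | 0.96–0.99 |
| Single forest, arm a predictor | 40% | 8.3–11.3% | 0.35–0.36 | 0.77–0.81 |
| Single forest, arm left out | 40% | 7.2% | not run | 0.80 |
| Single forest, separately by arm | 40% | 25% | 0.51 | 0.78 |
| Pooled forest, 10 imputations, Rubin's rules | 40% | 1.0% | 0.35 | 0.97–0.98 |
| Single forest, arm a predictor | 14% | 6.1% | 0.45 | 0.92–0.94 |
| Single forest, separately by arm | 14% | 8.6% | not run | 0.93 |

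The type I range for the single forest with arm as predictor covers correlations 0.3, 0.5 and 0.7 and one setting with loss depending on baseline. The effect runs used correlation 0.5 only.

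**Consistency.** In simulation B at correlation 0.5, the SE ratio is 0.207/0.238 = 0.87. The effective cut-off is 1.96 × 0.87 = 1.71, a two-sided error of about 8.8%, in line with the simulated 8.3%.

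**Cohen's d.** At 40% loss, numerator and denominator shrink together: 0.45–0.46 for a true 0.50, about 10% low.

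**Future sample size.** n per arm = 2 × (2.8016 × SD/Δ)², two-sided 5%, 80% power:
- Δ 0.36, SD 1: 121.1, so 122.
- Δ 0.36 from outside, SD 0.79 from the pilot: 75.6, so 76.
- Δ 0.27 and SD 0.79, both from the pilot: about 134.
- Δ 0.50, SD 1: 63. With SD 0.79: 40. From the shrunken d of 0.45: 78.

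The error runs in either direction, depending on which pilot estimates are carried forward.

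**The case against.** Single imputation is an inference. The sentence does not exclude a multiple version, and an article may leave the number of imputations and the pooling rule to a fuller plan. This stands: the type I error and SD results are conditional, and under pooled imputation they disappear. What it does not answer is the choice of the forest itself, which the article does state. With arm as an ordinary predictor, pooling left the 0.50 effect at 0.35, and power was 7% against 28% for complete cases.

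A reader might take 40% loss as planned and conclude that type I error doubles. The same sentence's 38 completers imply 14% loss, where there is no doubling.

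A reader might also infer that the randomised trial would be underpowered. The documents do not support this. It requires pairing an external raw difference with the pilot's imputed SD, and the article says only that the data will inform power calculations. It names Cohen's d as its effect measure, and d points to a larger trial, not a smaller one.

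The sizes also depend on forest settings and predictors. Session-level ratings, which the simulations omit, could sharpen the predictions, although the Abstract places the per-session evaluation in the intervention group.

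Finally, arm coincides with clinic, as the Discussion concedes, so no between-arm p-value here is confirmatory. That lowers the severity; it does not make the imputation sound.

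**Conclusion.** The point holds in conditional form. If the imputation gives one completed data set treated as observed, type I error is about 8–11%, the SD about 20% low and the raw effect about 25–30% too small at 40% loss. At 14% loss, type I error is about 6%, the SD 6–8% low and the raw effect about 10% low. If imputations are pooled, type I error is no longer inflated and the SD recovers, but the shrinkage remains unless arm is handled explicitly. Imputing each arm separately removes the shrinkage, but without pooling it raises type I error to 25% at 40% loss.

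These figures rest on the assumed correlations, on loss that is random or depends on baseline, and on the forest settings used. Two separately built simulations agree on them. The claim is that the pilot's inputs to the next trial may be distorted, not that they err in a known direction. Severity: should be fixed, given a non-randomised pilot.

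**What to change.** 1. Replace the imputation sentence. Preferred: analyse MFQ at T2 and T3 in one likelihood-based repeated-measures model with arm, visit, arm × visit and T1 MFQ as covariate. T1 should not also be an outcome. This needs no imputation of outcomes under missing at random.
2. Alternatively, use multiple imputation with arm forced into the imputation model, and pool by Rubin's rules. State the number of imputations and the predictors.
3. Take SDs for planning the randomised trial from observed values only.
4. Reconcile 60% retention with 38 completers: 44 at 60% gives about 26, and 38 of 44 is about 86%.

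Neither replacement was itself simulated. The nearest method checked is complete-case ANCOVA, which stayed near nominal and unbiased in the settings run. A patient missing both T2 and T3 contributes no outcome to the mixed model, so its results should lie close to that.

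The cost is analysis wording; standard software suffices, and conduct, data collection and participants are unaffected. The downside is that standard errors, and any intervals reported, become wider.

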### Randomization, allocation concealment, and blinding

Assignment to the two study arms is non-randomized and the allocation is not blinded. The pre- and post-assessments will not be blinded, but rather done by trained psychotherapists who are independent and did not provide treatment in either of the study arms to the respective families.

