### Outcomes

Assessments are at pre-treatment (T1), post-treatment (T2) and follow-up at 6 months (T3) (see Fig. 1 for overview). Assessments are face-to-face (clinical interview) or paper-pencil questionnaires and filled out by index patients and/or their caregivers/significant others.

Primary outcomes are, first, the feasibility of the CBASP@YoungAge treatment program. This includes both practicability in the outpatient setting for therapists and suitability for patients and family members, primarily measured by continuous process evaluation (therapists, patients, parents), therapist adherence, patient dropout rate, and recruitment rate during the study and treatment. Second, change in depressive symptomatology between pre- and post-assessment is a primary endpoint, with change measured by the clinical interview (child DIPS, parent or child version) and the Mood and Feelings Questionnaire (MFQ).

Secondary outcomes are the interpersonal behavior between caregiver and children (Impact-Message-Inventory for children and adolescents, IMI@YA), the global health of both caregivers and participating children (KIDSCREEN; Positive mental health questionnaire, PMH), parents' mental health (Brief-Symptom-Inventory, BSI), and parenting quality (Parenting Questionnaire, EFB).

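### ANCOVA is named for the pre-post test within the intervention arm, a task that its usual baseline-adjusted form does not perform

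*Protocol article*

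**What the plan says.** The Statistical analysis section of the protocol article gives ANCOVA two jobs in one sentence. The first is within one arm: "ANCOVA models will be used to test the pre- and post-differences in the intervention group". The second is between arms: "the difference between intervention and control group after the intervention and at follow up". Both come under analyses of effectiveness. The section names no covariate, does not say whether time is a repeated factor, and names no paired or mixed model. It adds that "Within or between-group effect sizes (Cohen’s *d*) will be calculated".

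The Outcomes section makes the quantity important: "change in depressive symptomatology between pre- and post-assessment is a primary endpoint", measured by the Kinder-DIPS interview and the MFQ. On design, the article states that "Assignment to the two study arms is non-randomized and the allocation is not blinded". Its Discussion concedes that each clinic treats only one arm, so site effects cannot be excluded.

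**The concern.** ANCOVA usually compares groups on the post-treatment score after adjustment for baseline. That is a sound choice for CBASP@YoungAge against treatment as usual. Within the intervention arm alone there is no group term, so the method named has no contrast that corresponds to mean change. An analyst who follows the sentence must improvise, and the obvious ways of doing so err in opposite directions. The choice could decide whether change on a primary endpoint is reported as significant. The article also says that the data will inform power calculations for a later randomised trial, so a wrong within-arm standard error could carry forward.

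There is also a point of interpretation. Patients enter because they currently meet criteria for a depressive disorder. Natural course and regression to the mean therefore contribute to any uncontrolled change, yet the test is listed as evidence on effectiveness.

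**Working it through.** The article gives no significance level, standard deviation, pre-post correlation or power for this test, so there is no stated figure to reproduce. The check asks how each plausible set-up behaves as a test of mean change.

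**Inputs from the article.** The planned arm size is 22: "We aim to recruit 44 participants (22 per treatment arm". Smaller arms were also checked because of the retention statement: "Assuming a 60% retention rate during the trial [56], this will lead 38 treatment completers with complete data". The 38 completers give 38/2 = 19 per arm, whereas 60% of 22 gives 0.60 × 22 = 13.2, about 13.

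**Assumptions.** Pre-post correlation r = 0.3, 0.5 and 0.7; equal pre and post SDs; normal scores; complete data; two-sided 5% test. Type I errors come from simulation with no true mean change (40,000 replicates). All standard errors are in SD units at n = 22.

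**Reference: paired analysis.** SE = √(2(1−r)/n).
- r = 0.3: √(1.4/22) = 0.252
- r = 0.5: √(1.0/22) = 0.213
- r = 0.7: √(0.6/22) = 0.165

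Type I error is 0.049 to 0.051 at n = 13, 19 and 22.

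**Set-up 1: time as an ordinary (independent) factor.** SE = √(2/n) = √(2/22) = 0.302 at every r. The ratio to the reference is 1/√(1−r) = 1.20, 1.41 and 1.83. Type I error is 0.021, 0.007 and 0.001, so the test is conservative. For a true change of 0.5 SD at r = 0.5, power is 0.32, against 0.61 for the paired test.

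**Set-up 2: change regressed on baseline centred at its sample mean, testing the intercept.** SE ≈ √((1−r²)/n).
- r = 0.3: √(0.91/22) = 0.203
- r = 0.5: √(0.75/22) = 0.185
- r = 0.7: √(0.51/22) = 0.152

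The ratio to the reference is √((1+r)/2) = 0.81, 0.87 and 0.92. What is lost is the sampling variation of the baseline mean, (1−r)²/n. Adding it back gives (1−r²)/n + (1−r)²/n = 2(1−r)/n, the paired variance. As a test of population mean change, type I error is 0.107, 0.085 and 0.069, so it is anti-conservative.

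**Set-up 3: the same with uncentred baseline.** The intercept is now the expected change for a patient whose baseline score is zero. If the baseline mean lies 2.5 SD above zero (an assumption), that quantity equals 2.5 × (1−r) = 1.75, 1.25 and 0.75 SD even when mean change is nil. The null is rejected in 0.82, 0.63 and 0.40 of replicates. This is the wrong hypothesis, not just a wrong standard error.

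**Set-up 4: repeated-measures ANCOVA, time within patient, centred covariate other than baseline (age, for example).** Type I error is 0.049 to 0.050, which is valid. Centring matters: with that covariate left uncentred and its mean 5 SD above zero (an assumption), power for the 0.5 SD change at r = 0.5 falls from about 0.61 to about 0.07.

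The pattern is the same at n = 19 and n = 13. At r = 0.5, for example, set-up 1 gives 0.007 and 0.009, and set-up 2 gives 0.085 and 0.084.

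**The case against.** The strongest reply is that this is one sentence in a condensed article. It speaks of ANCOVA models in the plural, excludes no error structure and refers to within-group effect sizes, so the authors may well intend a repeated-measures analysis. Set-up 4 shows that such a form is valid, and a full analysis plan may specify it. Each faulty result above appears only after a set-up has been chosen that the article does not state, and the correlations are assumed.

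Much of this stands. A reader might infer that ANCOVA can never give a within-arm pre-post test, or that its standard error would be undefined. The document does not support either inference: set-up 4 works, and a standard error exists in every set-up. Nor can one say which way the error would go.

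The reply does not remove the point, because the finding is not a missing detail. The article names a method whose usual form does not fit one of the two tasks assigned to it. The valid form needs a repeated factor and a centred non-baseline covariate, and the text mentions neither. Using one label for both tasks makes the baseline-adjusted reading the natural one.

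It is also fair to say that the within-arm test is not the only planned analysis of the endpoint. The same sentence plans the between-arm comparison, the objective speaks of potential effectiveness, and the Discussion discloses the quasi-experimental design and the site and seasonal effects.

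**Conclusion.** The concern holds as a misfit between the named method and one of its two tasks. Of the set-ups examined at n = 22 and r = 0.3 to 0.7, one is conservative (type I error about 0.02 to 0.001), one is anti-conservative (about 0.11 to 0.07), one tests the wrong hypothesis, and only the repeated-measures form with a centred non-baseline covariate is valid. The sizes rest on the assumed correlations, equal SDs and complete data; the directions do not depend on which r in that range applies.

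A reader might go further and conclude that the planned analysis of the primary endpoint is invalid. The document does not support that. The within-arm test is one of the planned tests of that endpoint, and the between-arm use of ANCOVA is untouched by this point. Separately, a significant within-arm change would not by itself show an effect of CBASP@YoungAge, whichever test is used.

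**What to change.** Split the sentence in Statistical analysis into two.

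- **Within-arm change in MFQ:** replace ANCOVA with a paired t interval for post-treatment minus pre-treatment, or a repeated-measures mixed model over the three assessments with unstructured covariance. Report the mean change with a 95% confidence interval and label it descriptive, because natural course and regression to the mean contribute to it.
- **Between-arm contrast:** keep ANCOVA adjusted for the baseline score, at post-treatment and at 6-month follow-up. Base any effectiveness statement on this contrast, and state the non-randomised, site-confounded design as a limitation beside it.

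If a mixed model is used, its arm-by-time term should not be presented as the baseline-adjusted contrast. It estimates a difference in change, and the two can differ when arms are not randomised. Both analyses should use the set already planned: "Data will be analyzed based on the Intention-to-treat (ITT) sample".

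The cost is a change of wording, with no extra patients, assessments or data.

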**Method:**

This quasi-experimental pilot feasibility trial is a phase 1 to phase 2 study investigating the feasibility and effectiveness of CBASP@YoungAge by including an intervention group (CBASP@YoungAge) and a treatment-as-usual control group. The treatment of depressive symptoms as well as interpersonal problems with primary caregivers are the main targets of CBASP@YoungAge. Personalization is ensured concerning the treatment course, caregivers’ involvement, and the patient’s age. The primary outcome relates to two areas: the feasibility of the CBASP@YoungAge treatment program in an outpatient context and a change in patients' depressive symptomatology from before to after treatment. We conduct a brief process evaluation after each session in the intervention group to closely monitor the treatment process and examine feasibility from the therapists' and patients' perspectives and mechanisms of symptom change. In addition, we consider interpersonal behavior between children and caregivers, parenting behavior, and monitor the global-health-index in children and parents as secondary outcomes. Pre-, post-, and follow-up data are evaluated.

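### Effectiveness could be read from an uncontrolled pre-post d in the CBASP arm, because within-group and between-group d share one size scale and the CBASP-minus-TAU difference is not named as the effectiveness estimate

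*Protocol article*

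**What the plan says.** All analysis statements below are in the Statistical analysis section of the protocol article, in the paragraph on effectiveness.

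- **Within-arm test:** "ANCOVA models will be used to test the pre- and post-differences in the intervention group". No such test is named for TAU.
- **Between-arm test:** the same sentence also plans to test "the difference between intervention and control group after the intervention and at follow up".
- **Effect sizes:** "Within or between-group effect sizes", as Cohen's d, "will be calculated and interpreted according to standard conventions". Both kinds are read on one scale: "< .50 = small; .50–.80 = medium; > .80 = large". Within-group d is not restricted to one arm.
- **Description:** "Summary statistics will be used as appropriate to describe and compare data for all participants".

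The Abstract (Method) words the effectiveness half of the primary outcome as "a change in patients' depressive symptomatology from before to after treatment". The Outcomes section likewise makes the change from pre- to post-assessment a primary endpoint. Neither place says whether this means change within the CBASP arm or a difference in change between arms. The Objective section does separate the two ideas: aim 2 concerns change during treatment, and aim 3 expects greater alleviation than under TAU.

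On entry, "Inclusion is based on a structural clinical interview", so patients are enrolled because they meet criteria for a depressive disorder at T1. The limitations paragraph of the Discussion names the non-randomised design, site effects and seasonal effects. It does not name regression to the mean or spontaneous recovery.

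**The concern.** A between-group d and a pre-post d measure different things. The first removes whatever improvement the two arms share. The second keeps all of it: regression to the mean after selection on current depression, natural recovery, and the non-specific effect of attending any therapy. Verbal labels suited to the first cannot be carried over to the second.

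Three features of the text combine. The pre-post test in the CBASP arm comes first among the tests listed under effectiveness. A pre-post d receives the same size words as a controlled d. The primary effectiveness endpoint is itself worded as pre-post change. A report could thus present a labelled, uncontrolled within-arm d as the primary effectiveness result without departing from the plan. The data are also meant to inform power calculations for a later randomised trial, so confusing the two quantities could carry forward into that trial's target effect.

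**Working it through.** The plan states no SD, pre-post correlation, target effect or significance level for this analysis, so there is no figure of its own to reproduce. From the documents come 22 patients per arm and the cut-offs .50 and .80. Everything else below is an assumption, shown as a range.

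**1. Shared improvement, no difference between arms**

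Let both arms improve by c, in units of the baseline SD, with equal SDs at T1 and T2 and pre-post correlation r.

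- Between-group d = c − c = 0.
- Within-group d on the raw SD = c.
- Within-group d on the SD of change = c / √(2(1 − r)). At r = 0.5 this equals c.
- The two-sided 5% paired test has noncentrality c√n at r = 0.5. For n = 22, c = 0.5 this is 0.5 × 4.690 = 2.35, against a critical t of 2.080 on 21 df.

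Two smaller sample sizes are shown because the section on participants and sample size is not consistent about completers. Its stated 38 completers give 19 per arm, while its 60% retention gives 22 × 0.60 = 13.2 per arm. The point does not depend on which is right.

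| Shared change c | Label on the plan's scale | P(significant), n = 22 | n = 19 | n = 13 |
|---|---|---|---|---|
| 0.5 | medium | 0.61 | 0.54 | 0.38 |
| 0.7 | medium | 0.88 | 0.82 | 0.64 |
| 0.9 | large | 0.98 | 0.96 | 0.85 |

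The true between-group d is 0 in every row.

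**2. Regression to the mean alone**

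Assume no true mean change. Patients are the top fraction p of a reference population on the T1 interview, the interview correlates a with the MFQ, and the MFQ has retest correlation b. With z the normal cut-point for p, i = φ(z)/p and k = i(i − z), the expected within-arm d on the T1 SD is

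d = a(1 − b)i / √(1 − a²k).

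Example: p = 0.20, a = 0.6, b = 0.7 gives i = 1.400 and k = 0.781, so d = 0.6 × 0.3 × 1.400 / √(1 − 0.36 × 0.781) = 0.30.

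| Selection p | a | b | Range of d |
|---|---|---|---|
| top 5 to 20% | 0.6 to 0.8 | 0.5 to 0.7 | 0.30 to 1.23 |
| top 5 to 20% | 0.6 to 0.8 | 0.8 | 0.20 to 0.49 |
| top 50% | 0.6 to 0.8 | 0.5 to 0.7 | 0.16 to 0.41 |
| top 70% | 0.6 to 0.8 | 0.5 to 0.7 | 0.10 to 0.24 |

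Regression alone can therefore reach the medium or large label under strong selection with a retest correlation of 0.7 or less, but stays below .50 in the other rows.

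**3. How well the TAU comparison would show it**

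The approximate 95% half-width for an unadjusted between-group d is 1.96√(2/n): 0.59 at 22 per arm, 0.64 at 19 and 0.77 at 13. Baseline adjustment at r = 0.5 multiplies this by √(1 − 0.25) = 0.866, giving 0.51 at 22 per arm. The Background cites a pooled effect of 0.36 for psychotherapy in this population, so the interval cannot separate zero from that value.

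**The case against.** A reader might infer that the plan will call the within-arm d a treatment effect, or that it leaves the TAU data unused. The documents support neither reading. The text attaches only size words to d. The sentence naming the pre-post test also plans the comparison with TAU, summary statistics cover all participants, and within-group d is not confined to the CBASP arm. The Objective section keeps change during treatment apart from superiority over TAU. If both arms improve equally, the planned comparison is centred on zero and would show it. All of this stands.

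It would also be wrong to speak of untreated improvement. TAU is guideline-based psychotherapy and no arm is untreated, so the TAU contrast removes shared change but cannot measure what would happen without treatment.

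The regression figures depend on the assumed selection. The Recruitment section describes consecutive clinic patients selected by diagnosis and states no percentile. With weaker selection the same formula gives only about 0.1 to 0.4. A retest correlation over months of treatment may also already absorb some real change, so natural recovery cannot simply be added on top.

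Finally, a pilot may report within-group d descriptively, and the choice of standardiser is ordinary analysis-plan detail; it is not part of this point. What remains is that the document fixes a reading rule that merges two different quantities, and does not say which one carries the effectiveness conclusion.

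**Conclusion.** The point holds as a matter of interpretation, and correcting it is worthwhile though moderate in weight for a non-randomised pilot. As written, the plan permits an uncontrolled, size-labelled within-arm d to stand as the primary effectiveness result. It does not require that, and it does plan the controlled comparison.

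The size of the risk rests on assumed inputs. With a shared improvement of 0.5 to 0.9 SD, r = 0.5 and a true between-group d of 0, the CBASP pre-post test at n = 22 is significant with probability 0.61 to 0.98, and the change is labelled medium to large. Regression to the mean alone contributes about 0.1 to 0.4 under weak selection and about 0.3 to 1.2 under top 5 to 20% selection. The conclusion does not need the upper end of that range, since shared improvement from any source has the same consequence. The comparison with TAU is the safeguard, but it is imprecise and has no stated priority, so a null comparison beside a large pre-post effect is a foreseeable misreading.

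**What to change.** In the effectiveness paragraph of the Statistical analysis section:

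1. Name the baseline-adjusted CBASP-minus-TAU difference, with its 95% CI, as the effectiveness estimate, and apply the small/medium/large labels to that d only.
2. Report mean change from T1 to T2 and from T1 to T3, with 95% CI, side by side for both arms and without size labels. Do not add a separate significance test within TAU, because setting two within-arm tests against each other is not a comparison of the arms.
3. State that no conclusion on effectiveness is drawn from within-arm change.

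Align the wording of the primary effectiveness outcome in the Abstract (Method) and in the Outcomes section, so that both name the between-arm contrast.

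The cost is a few sentences and one table column from data already collected. The within-arm result loses its size label. The estimate that replaces it is imprecise and stays open to the site and season confounding that the Discussion acknowledges, so the pilot will support only a cautious statement on effectiveness.
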